### Procedure

The procedure for this study is shown in Fig 4. Participant ID numbers will be randomly assigned to the benign or pain modification group before data collection begins. After having read the information sheet and signed the consent form, participants will first complete the questionnaire battery. Following this, participants will complete the pain-threshold measurement task to assess their hot and cold pain thresholds. Next, participants will complete the Ambiguous Scenarios Task aiming to modify their biases towards pain-related or benign interpretations of ambiguous stimuli, according to their randomised group. Immediately following this, participants will complete the Interpretation of Ambiguous Sensation Task. All participants will then complete the battery of cognitive bias tasks. The test phase of the Ambiguous Scenarios Task will be completed first. The order of the sentence generation task and visual-probe task will be randomised and counterbalanced across participants, with the free recall memory bias task conducted last. Lastly, those randomised to the pain modification condition will complete the bias repair task. Participants will complete the study in a single session lasting approximately two hours minutes. Following completion of the study, participants will be thanked and debriefed. The entire experiment will take approximately 120 minutes to complete.

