### Procedure

The procedure for this study is shown in Fig 2. Participant ID numbers were randomly assigned to the benign or pain modification group before data collection began via Random.org. After having read the information sheet and signed the consent form, participants completed the self-report measures. Following this, participants completed the heat pain-threshold task. Next, participants completed the Ambiguous Scenarios Task aiming to modify their biases towards pain-related or benign interpretations of ambiguous stimuli, according to their randomised group. This was immediately followed by the test phase of the Ambiguous Scenarios Task, then the Incidental Learning Task and the Sentence Generation Task. Participants then completed the ISSA. At the end of the experiment, participants in the pain-related CBM-I group completed 30 trials of the benign modification to ensure that they did not experience lasting effects of pain-related bias modification, before being thanked and debriefed. The entire experimental duration was approximately 90 minutes.

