### Primary and secondary outcomes

The primary outcomes in this study are pain intensity and unpleasantness for ambiguous somatosensory sensations as assessed via the ISSA paradigm. Secondary outcomes are (i) pain-related interpretation biases for ambiguous words and scenarios as assessed via the Ambiguous Scenarios Task and Sentence Generation Task respectively, (ii) pain-related attentional and memory biases as assessed via the visual-probe task and surprise free-recall task respectively, and (iii) anxiety (State-Trait Anxiety Inventory), depression (Beck Depression Inventory-II), anxiety sensitivity (Anxiety Sensitivity Index-3), somatosensory amplification (Somatosensory Amplification Scale), pain catastrophising (Pain Catastrophising Scale), intolerance of uncertainty (Intolerance of Uncertainty Scale-12 Item), and handedness (Edinburgh Handedness Questionnaire – Short Form).

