### Quantitative sensory testing

#### Pain threshold measurement.

A similar procedure to the pilot study will be followed to assess each participant’s individual pain threshold, although in additional to heat pain thresholds cold pain thresholds will also be assessed the TSA-II previously described For both hot and cold trials the thermal stimulus will increase by 1°C/second from its baseline temperature of 32°C until the participant indicates the very first moment they feel the temperature as painful by pressing the left mouse button. The thermal stimulus has upper and lower safety limits of 53°C and 0°C. The thermal stimulus decreases by 8°C/second back to baseline temperature. Three hot and three cold trials will be conducted, with a 10-second inter-trial interval. The pain threshold measurement will take approximately 10 minutes.

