#### Interpretation of somatosensory sensations assessment.

In addition to ambiguous heat stimuli discussed previously, the main experimental study will also assess interpretation of ambiguous cold stimuli administered to the non-dominant hand using the TSA-II. Specifically, cold stimuli at 60%, 80%, 100%, 120% and 140% of an individual’s cold pain threshold will be presented three times each, in a random order set across participants. Percentage threshold temperature values exceeding the safety limits of the TSA-II will be capped at 0°C (i.e., the TSA-II’s safety limits). Each cold trial will begin with the thermal stimulus decreasing from baseline temperature at a rate of 1°C/second until reaching the target temperature. The target temperature will be held for three seconds before returning to baseline at a rate of 8°C/second. At this point, participants will rate via pen and paper visual analogue scales the intensity (from 0 no sensation to 100 most intense pain you can imagine), and the unpleasantness (from 0 not unpleasant at all to 100 extremely unpleasant) of the stimulus. The fifteen cold trials will be presented consecutively with a 10 second inter-trial interval. The order of heat and cold pain trials will be randomised across participants, with the thermode removed for three minutes between each block of trials. This task will take approximately 20 minutes to complete

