Descriptive statistics will be computed for demographic characteristics, self-report measures (scored according to their instructions), cognitive bias task scores (Ambiguous Scenarios Task test phase, Sentence Generation Task, Visual-Probe Task and free recall task) and responses on the Interpretation of Ambiguous Somatosensory Sensations Task. Differences between the benign and pain modification groups will be conducted using independent samples *t*-tests and mixed-design ANOVAs where appropriate. Should any statistically significant differences be observed between groups on demographic or self-report measures, analyses will be conducted controlling for these (e.g., Analysis of Covariance). Pearson’s correlation coefficients will be conducted between outcomes on the self-report measures, cognitive bias scores and interpretation of ambiguous sensations ratings. As thermal pain sensitivity is associated with age (e.g., [88–90]), Pearson’s correlation coefficients will also be computed between age and interpretation of ambiguous sensations ratings. Should these be statistically significant, then age will be controlled for as a covariate where appropriate in the statistical analyses. The moderating effects of visual imagery and intolerance of uncertainty on the association between group and interpretation bias scores from the Ambiguous Scenarios Task will be investigated using linear multiple regression models. Similarly, linear multiple regression models will be used to test the effect of group on interpretation bias measures while controlling for other variables that differ between groups.

Data from the Ambiguous Scenarios Task, Sentence Generation Task and ISSA will be processed as discussed above for the pilot study. The only difference is that for the Sentence Generation Task, two raters will independently and blindly categorise participant response sentences as either pain-related (e.g., *He had a pressing pain in his head*) or benign (e.g., *The boy was pressing the buttons in the lift*). The initial inter-rater agreement will be computed, and any disagreements between raters will be discussed in order to reach consensus (involving a third independent member of the research team if necessary).

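### The arm is fixed to the participant ID before consent, questionnaires and threshold measurement, although it is not needed until training starts; the pilot used the same scheme and its arms differed widely before training

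*Protocol article*

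**What the plan says.** Main study, Procedure: "Participant ID numbers will be randomly assigned to the benign or pain modification group before data collection begins". Participants then read the information sheet, consent and complete the questionnaires. "Following this, participants will complete the pain-threshold measurement task to assess their hot and cold pain thresholds". Training follows, then the ISSA, then the cognitive bias tasks. Last comes a bias-repair task for the pain arm only.

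The threshold is the temperature reached on a device ramp, which runs "until the participant indicates the very first moment they feel the temperature as painful by pressing the left mouse button". It sets the ISSA stimuli: "cold stimuli at 60%, 80%, 100%, 120% and 140% of an individual’s cold pain threshold will be presented three times each". Heat stimuli follow the same percentages. Targets beyond the device limits are capped.

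Primary and secondary outcomes: "The primary outcomes in this study are pain intensity and unpleasantness for ambiguous somatosensory sensations as assessed via the ISSA paradigm". These are pen-and-paper visual analogue ratings.

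The only masking described is for the Sentence Generation Task, a secondary outcome, where "two raters will independently and blindly categorise participant response sentences". On imbalance, the analytic plan says: "Should any statistically significant differences be observed between groups on demographic or self-report measures, analyses will be conducted controlling for these". Age is handled by a similar conditional rule. The pain threshold is not named.

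The pilot allocated in the same way: "Participant ID numbers were randomly assigned to the benign or pain modification group before data collection began via Random.org".

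**The concern.** The arm is needed only when the Ambiguous Scenarios training begins. Fixing it to the ID earlier puts three steps after allocation that could come before it: enrolment, the questionnaires, and the measurement that sets the primary stimuli. If the person who issues IDs or runs the session can read the list, knowledge of the arm could affect who receives which ID, how the baseline tasks are conducted, and how the ISSA is run. With a subjective primary outcome, some of these effects could pass for a training effect.

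The pilot gives a reason to take this seriously. Its questionnaires preceded training, so randomised arms should differ only by chance, yet one scale linked to the primary ratings separated them widely. The section on insights for the main study lists the pilot's lessons and five changes. It does not mention this imbalance, and the allocation scheme is carried forward.

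**Working it through.** **1. The plan's own figures.** Inputs from the main-study Participants section: f = 0.244, two-sided alpha 0.05, two groups. With noncentrality f²N and df 1 and N − 2, N = 134 gives 0.0595 × 134 = 7.98 and power 0.8006; N = 132 gives 0.7946. The stated 134 is reproduced, and the time at which the arm is released does not enter it. Table 3's Cohen's d for unpleasantness also reproduces: 11.78/12.38 = 0.95 at 60% and 15.26/15.22 = 1.00 at 80%.

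**2. Pilot imbalance before training.** Inputs from Table 2, n = 9 per arm, ASI-3 total: benign 13.22 (SD 5.63), pain 30.00 (SD 8.03).

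- Pooled SD = √((5.63² + 8.03²)/2) = 6.93
- d = 16.78/6.93 = 2.42
- t(16) = 16.78/(6.93 × √(2/9)) = 5.13, p = 0.00010 (Welch 0.00014)
- As the smallest of the 16 tabulated scores: 1 − (1 − 0.00010)^16 = 0.0016, about 1 in 600
- As the smallest of seven total scales: 0.0007, about 1 in 1,400

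Seven of the 16 rows have p < 0.05: four from the ASI-3 and three from the PCS, all higher in the pain arm. Subscales and their own totals are counted together, so these are not seven independent signals. BDI-II, FPQ-III and STAI-Trait are unremarkable; BDI-II and FPQ-III Medical are slightly higher in the benign arm.

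**3. Link to the primary ratings.** The pilot's correlational analyses report r = .51 between anxiety sensitivity and unpleasantness at both 60% and 80%. I assume that this refers to the ASI-3 total. Rebuilding the group correlations from Tables 2 and 3 gives r(group, ASI) = 0.79, and r(group, unpleasantness) = 0.45 at 60% and 0.47 at 80%. The partial correlation of group with rating, given ASI, is

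(r_yg − r_ya·r_ag) / √((1 − r_ya²)(1 − r_ag²)).

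- 60%: (0.451 − 0.51 × 0.789)/√(0.740 × 0.378) = 0.09
- 80%: (0.470 − 0.51 × 0.789)/√(0.740 × 0.378) = 0.13

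With 18 participants these are imprecise. They show that the imbalance could account for most of the pilot group difference at these two levels, not that it does.

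**4. Threshold route.** If the percentages apply to the Celsius reading, a 1 °C difference in recorded threshold moves uncapped targets by 0.6 to 1.4 °C. Pilot thresholds are not reported by arm. The only information by arm is the number above the 50 °C cap: 3 benign and 2 pain at 140%, 1 and 1 at 120%. This shows no separation.

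**5. Chance imbalance in the main study.** With 67 per arm, the standard error of a baseline difference is √(2/67) = 0.17 SD, so 95% of chance differences lie within about ±0.34 SD. A larger sample shrinks chance imbalance. It does not shrink imbalance caused by selection.

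**The case against.** The strongest reply is that a list made in advance and keyed to ID numbers is ordinary practice. It does harm only if someone who enrols participants or runs sessions can see it. The article does not say that anyone can, and a full protocol may describe concealment and masking. This stands: the point cannot be that concealment is absent. What remains is the stated timing, which exposes steps that do not need the arm.

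Several stronger readings are tempting, and the documents do not support them:

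- **That the pilot shows steered thresholds.** The imbalanced scores were completed before the threshold task, and the sparse threshold data by arm show no difference.
- **That the pilot shows selection.** Nothing in the stated order gives anyone an ASI-3 score before the ID is issued. Selection would have to act through something else related to anxiety sensitivity.
- **That the experimenter determines the threshold or attends the ratings.** The text describes a participant's button press and pen-and-paper scales. Experimenter influence is an inference.
- **That any leak would inflate the effect.** An earlier press on the heat ramp lowers the uncapped heat targets. In the pain arm that would, if anything, work against the hypothesis.
- **That nothing could be repaired.** The adjustment rule would cover an ASI-3 or PCS difference if it were significant, and the recorded threshold could serve as a covariate. Adjustment would not reach unrecorded selection or differences in how the session was run.

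**Conclusion.** The concern holds as a design risk. Allocation is fixed earlier than it needs to be, ahead of enrolment and of the measurement that scales the primary stimuli, and the article describes no protection for those steps. Whether bias follows depends on who can see the list, which the article does not say.

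The pilot is a warning and not a demonstration. Its ASI-3 imbalance (d = 2.42) would arise by chance about once in 600 after correction for 16 scores, and chance remains a possible explanation. It matters because the scale correlated with low-level unpleasantness ratings, and because the same scheme goes forward without comment. I cannot size any resulting bias in the main study from the documents. The figures rest on Table 2's rounded means and SDs, on approximately normal scores, and on .51 referring to the ASI-3 total.

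**What to change.** In the main-study Procedure, issue IDs without an arm. Let the task software, or a sealed code, release the arm only when the Ambiguous Scenarios training starts, after the questionnaires and both thresholds have been recorded. Run the training and the ISSA under a neutral code, so that the session runner learns the arm only at the final bias-repair step. The existing task order already permits this, because bias repair is the only later step that differs by arm.

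If the full protocol already conceals the list and masks the session runner, the Procedure should say so; late release would still give better protection.

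The cost is a procedural amendment and minor programming, and the session runner must not watch the training screen. No participant, visit or staff member is added, and the sample size stays at 134.

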### Data reduction and analytic plan

Data will be analysed using SPSS for Windows 29. For all analyses the significance level will be set to *p* = .05 and two-tailed. Standardized procedures will be followed for identifying and handling missing data and outliers [85]. Visual inspection and descriptive statistics will be performed to identify missing data, and should they exist missing data analysis performed. If <  10% of data is missing and the data is missing at random or completely at random, multiple imputation by chained equations will be used [86,87]. Datasets will be inspected for outliers using box and whisker plots inspect for univariate outliers, and Mahalanobis distance (*D*^*2*^) to detect multivariate outliers [85]. Should outliers exist, their cause will first be established, and if resulting from unique cases or data anomaly, will either be removed or transformed (e.g., log transformation, square root transformation) as appropriate prior to final analysis of the dataset [85].

Descriptive statistics will be computed for demographic characteristics, self-report measures (scored according to their instructions), cognitive bias task scores (Ambiguous Scenarios Task test phase, Sentence Generation Task, Visual-Probe Task and free recall task) and responses on the Interpretation of Ambiguous Somatosensory Sensations Task. Differences between the benign and pain modification groups will be conducted using independent samples *t*-tests and mixed-design ANOVAs where appropriate. Should any statistically significant differences be observed between groups on demographic or self-report measures, analyses will be conducted controlling for these (e.g., Analysis of Covariance). Pearson’s correlation coefficients will be conducted between outcomes on the self-report measures, cognitive bias scores and interpretation of ambiguous sensations ratings. As thermal pain sensitivity is associated with age (e.g., [88–90]), Pearson’s correlation coefficients will also be computed between age and interpretation of ambiguous sensations ratings. Should these be statistically significant, then age will be controlled for as a covariate where appropriate in the statistical analyses. The moderating effects of visual imagery and intolerance of uncertainty on the association between group and interpretation bias scores from the Ambiguous Scenarios Task will be investigated using linear multiple regression models. Similarly, linear multiple regression models will be used to test the effect of group on interpretation bias measures while controlling for other variables that differ between groups.

Data from the Ambiguous Scenarios Task, Sentence Generation Task and ISSA will be processed as discussed above for the pilot study. The only difference is that for the Sentence Generation Task, two raters will independently and blindly categorise participant response sentences as either pain-related (e.g., *He had a pressing pain in his head*) or benign (e.g., *The boy was pressing the buttons in the lift*). The initial inter-rater agreement will be computed, and any disagreements between raters will be discussed in order to reach consensus (involving a third independent member of the research team if necessary).

For the Visual-Probe Task, practice and experimental trials with incorrect responses will be excluded from the analyses. Box and whisker plots for overall data will be inspected to identify response time outliers which will be removed. Mean response times for each participant will then be calculated, with any response time three standard deviations above or below this mean also removed as outliers. Attentional bias scores will then be calculated for each participant at each exposure duration (i.e., 500ms and 1250ms) using the following formula:

$$\text{Attentional bias score=}\left(\left(\text{TuPl – TlPl}\right)\text{+}\left(\text{TlPu – TuPu}\right)\right)\text{/2.}$$

Where T =  threatening stimulus, P =  probe, u =  upper position, l =  lower position.

A positive bias score indicates a shift of attention towards the location of threatening words relative to neutral words. A negative bias score indicates a shift of attention away from the location of threatening words towards neutral words [62]. For the free recall memory bias task, the proportion of accurate words recalled per stimuli category will be computed and used in the analyses [44,70,91].

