For the Sentence Generation Task, sentences were categorised as pain-related or benign. The definition for pain-related interpretations was: ‘describes a painful experience or a situation usually associated with pain’; the working definition for benign interpretations was: ‘describes an experience or situation unrelated to pain’ [44,54]. The proportion of pain-related sentences out of total sentences generated was calculated, as in previous research [17].

For the ISSA, mean ratings of intensity and unpleasantness were calculated for each stimulus intensity. Ratings were excluded where the temperature required for the percentage of pain threshold could not be reached due to the safety limits of the TSA-II.

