### Aims and hypotheses

The primary aim of the main experimental study is to investigate the effects of pain-related CBM-I on the interpretation of ambiguous somatosensory stimuli in healthy, pain-free individuals. The secondary aim is to investigate the effects of CBM-I on patterns of pain-related interpretation, attentional and memory bias. A between-groups design will be implemented, randomising healthy participants to benign CBM-I or pain CBM-I conditions. It is hypothesised that:

Participants in the pain modification group will interpret somatosensory stimuli at levels around the pain threshold as more intense and unpleasant than participants in the benign modification group.Participants in the pain modification group will have higher levels of pain-related interpretation bias for ambiguous words and scenarios, as compared to the benign modification group. This is operationalised by:a. In the Ambiguous Scenarios Task, participants in the pain modification group will be more likely to interpret ambiguous scenarios as pain-related, as compared to participants in the benign modification group.b. In the Sentence Generation Task, participants in the pain modification group will generate more pain-related sentences than participants in the benign modification group.Participants in the pain modification group will have higher levels of pain-related attentional and memory biases bias than participants in the benign modification group.

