### Participants

Ethical approval has been granted by University of Southampton Research Ethics Committee (ERGO ID: 92317). Eligibility criteria for inclusion are: (i) aged 18–50 years; (ii) normal or corrected to normal vision; and (iii) fluency in the English language. Exclusion criteria are: (i) diagnosis of any type of chronic pain or psychiatric condition; (ii) currently experiencing pain; or (iii) diagnosis or knowledge of any reading difficulties. Participants will be recruited using social media, word-of-mouth, and the website SONA which is used to recruit undergraduate psychology students at the University of Southampton. BSc Psychology students at the University of Southampton will receive partial course credit for participating. A power analysis was conducted using G*Power [82] to determine suitable sample size for an ANOVA, with a medium effect size based on the pilot study which revealed many of the intensity and unpleasantness ratings between benign and pain modification groups were of medium to large effect (effect size *f* =  0.244, α error probability =  0.05, power (1 – *β* error probability) =  0.80, numerator degrees of freedom =  1, and number of groups =  2). This indicates a sample size of 134 is required for these conditions to be met. The start date for this study is 1^st^ June 2024 and the planned end date as registered with the University of Southampton Research Ethics Committee is 1^st^ May 2026.

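### Two unranked primary ratings are each tested at .05 with no success rule or designated primary contrast, so the stated alpha of .05 and power of .80 do not both hold for the primary objective

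*Protocol article*

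**What the plan says.** All references are to the main-study part of the protocol article unless stated.

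- **Primary and secondary outcomes:** "The primary outcomes in this study are pain intensity and unpleasantness for ambiguous somatosensory sensations as assessed via the ISSA paradigm". Neither rating is placed first.
- **Aims and hypotheses:** the first hypothesis is that the pain modification group "will interpret somatosensory stimuli at levels around the pain threshold as more intense and unpleasant than participants in the benign modification group". It does not list the levels that count, or say whether one significant rating would confirm it.
- **Interpretation of somatosensory sensations assessment (ISSA):** "In addition to ambiguous heat stimuli discussed previously, the main experimental study will also assess interpretation of ambiguous cold stimuli". For the new modality, "cold stimuli at 60%, 80%, 100%, 120% and 140% of an individual’s cold pain threshold will be presented three times each"; heat uses the same five percentages.
- **Data reduction and analytic plan (pilot, carried forward to the main study for the ISSA):** "For the ISSA, mean ratings of intensity and unpleasantness were calculated for each stimulus intensity".
- **Data reduction and analytic plan (main study):** "For all analyses the significance level will be set to *p* = .05 and two-tailed". Group differences are to be examined by independent-samples t-tests or mixed-design ANOVAs as appropriate; neither method is assigned to an outcome.
- **Participants:** the power analysis uses f = 0.244, alpha 0.05, power 0.80, numerator df 1 and two groups. "This indicates a sample size of 134 is required for these conditions to be met".

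**The concern.** The sample-size statement describes one test. The outcome section and the alpha rule describe at least two. The protocol does not say which test the 80% power belongs to, or how the two ratings combine into a conclusion on the first hypothesis.

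With no success rule there are two readings. If either rating is enough, testing each at .05 gives more than a 5% chance of a false-positive primary conclusion. If both are needed, the false-positive rate is controlled, but the chance of success is below the stated 80%. Unless the two tests are perfectly correlated, neither reading delivers both stated figures.

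The lack of a designated contrast adds to this. Group differences in the pilot varied widely by stimulus level, so the conclusion could depend on which level or modality is emphasised after the data are seen.

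**Working it through.** **Inputs.** f = 0.244, alpha = .05, numerator df 1, two groups, N = 134 (Participants). Two primary ratings (Primary and secondary outcomes). Two modalities and five levels (ISSA section). Equal allocation is assumed, as no ratio is stated. The documents give no correlation between ratings, so the test statistics are assumed to correlate between 0 and .9.

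**1. The plan's own figure.** Noncentrality λ = N·f² = 134 × 0.244² = 7.978, with df 1 and 132. The noncentral F distribution gives power .8006 at N = 134 and .7977 at N = 133. So 134 is exactly right for one test at f = 0.244 (d = 2f = 0.488).

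**2. Either rating suffices.** For m independent tests, family-wise error = 1 − .95^m. Correlated cases use equicorrelated two-sided normal test statistics.

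| Tests | Correlation 0 | Correlation .5 | Correlation .9 |
|---|---|---|---|
| 2 (the two ratings) | 1 − .95² = 9.75% | 9.1% | 7.0% |
| 4 (rating × modality) | 1 − .95⁴ = 18.5% | 15.6% | 9.3% |
| 20 (rating × modality × level) | 1 − .95²⁰ = 64.2% | 41.8% | 15.5% |

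Only the first row follows from what the protocol states. The other two apply only if modalities, or modalities and levels, were tested separately and any significant result counted.

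If alpha were instead split equally (Bonferroni), the same noncentral F gives these results for each test:

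| Tests | Alpha per test | Power at N = 134 | N for 80% power |
|---|---|---|---|
| 2 | .025 | .711 | 164 |
| 4 | .0125 | .615 | 192 |
| 20 | .0025 | .402 | 256 |

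**3. Both ratings must succeed.** Each test has power .8006, assuming f = 0.244 for both ratings. Joint power at correlation 0 is .8006² = .641. With bivariate normal test statistics it is .688 at correlation .5, .714 at .7 and .751 at .9. Each test can stay at .05, because a false claim requires a rating with no effect to reach significance.

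**4. Does the choice of level matter?** Effect sizes printed in pilot Table 3:

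| Rating | 60% | 80% | 100% | 120% | 140% |
|---|---|---|---|---|---|
| Intensity | 0.69 | 0.82 | 0.19 | 0.30 | 1.95 |
| Unpleasantness | 0.95 | 1.00 | 0.67 | 0.31 | 3.02 |

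Intensity thus ranges from 0.19 at threshold to 1.95 at 140%. These come from nine participants per group. At 140%, five of the 18 could not reach the target temperature and such ratings were excluded, so that column is especially uncertain. The printed 1.95 is also larger than the tabulated means and SDs suggest: (70.75 − 52.6)/√((10.41² + 11.27²)/2) = 18.15/10.85 = 1.67. The spread across levels remains wide either way.

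**The case against.** **Test count.** A reader might infer four primary ANOVAs or twenty level-wise comparisons, and conclude that the false-positive rate is far above 5%. The documents do not support this. Mixed-design ANOVAs are named, and one such model per rating could carry level and modality as within-subject factors. Computing a mean for each level is data reduction, not a testing plan. The stated minimum is two tests, so 7–10% is the figure to lead with.

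**The word joining the ratings.** The first hypothesis links them with *and*. If that means both must succeed, type I error is not inflated at all. This is a fair reading, so inflation cannot be asserted unconditionally. But the protocol does not adopt that reading as a rule, and under it the stated power is too high.

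**Level of detail.** A condensed article may leave a testing hierarchy to an analysis plan. That would answer a complaint about missing detail. Here, however, the article itself fixes .05 for every analysis, names two co-equal primaries and quotes a power figure that fits one test. The conflict is among things it states.

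**Arithmetic.** The sample-size calculation contains no error; 134 is right for the test described. This stands.

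**Cost of a hierarchy.** Ranking the tests is not pure wording. Ratings are excluded where the target temperature could not be reached (in the pilot, 140% for five participants and 120% for two). A simple average over levels would therefore mix different levels in different participants. The Introduction also motivates the paradigm by asking whether training acts more below or above threshold, and a single main effect does not answer that. Both points stand and shape the fix.

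**Conclusion.** The point holds in a limited form. With two unranked primary ratings, .05 for every analysis and no success rule, the stated alpha and power do not both describe the primary objective. Either family-wise error is about 7–10%, or joint power is about 64–75%. The figures assume equal allocation, an effect of f = 0.244 on each rating for the power results, and a correlation between tests of 0 to .9. Only perfect correlation would remove the discrepancy.

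Error of about 9–19% (four tests) or 16–64% (twenty tests) is conditional on separate testing that the protocol does not state. The number of primary tests is undefined, not known to be large. The missing contrast still matters, because the pilot effects differ so much by level that a choice made afterwards could decide the result.

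**What to change.** Before any group data are seen:

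1. Name one primary contrast: the group main effect on one chosen rating, from a stated mixed model over pre-stated levels and both modalities, at two-sided .05. Use a model that tolerates the ratings excluded where the target temperature could not be reached.
2. Test the other rating at .05 only if the first is significant. This fixed sequence keeps family-wise error over the two ratings at or below 5% without splitting alpha.
3. Treat modality-specific, level-specific and interaction tests as secondary.
4. State that the 80% power applies to the first test only, and that f = 0.244 is the effect assumed for that contrast. If the intention is that both ratings must succeed, say so and restate joint power as about 64–75% at N = 134.

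**Cost:** with the fixed sequence N stays at 134. One rating must be ranked first, and the question of effects below versus above threshold becomes secondary.
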